# Safety assessment

According to French Legislation, the surveillance of studies with minimal risks and obligations is the same as that performed as part of normal care. Adverse events will be reported to the corresponding organisation’s pharmacovigilance, medical device vigilance or biovigilance. Note that no drugs are being tested in this study. Monitoring of the expected adverse effects will be specifically performed for the study.

Monitoring committee

Given the nature of the study (interventional study with minimal risks and obligations), no monitoring committee is envisaged.

# Description of the rules for permanent or temporary discontinuation

Discontinuation of a person‘s participation in the study

Patients enrolled in the study may request to withdraw from the study at any time and for any reason.

The investigator may temporarily or permanently discontinue a patient’s participation in the study for any reason which would be in the patient’s best interest.

A patient’s withdrawal from the study will not change the patient’s usual management.

If the patient is lost to follow-up, the investigator will do everything possible to contact the patient. In the event of early withdrawal from the study, the investigator must document the reasons as completely as possible in the medical record.

The data collected on patients who are lost to follow-up or have withdrawn from the study will be used at the time of the analyses.

If consent is withdrawn, and in compliance with regulations, the data will be used up to the date the consent was withdrawn.

Discontinuation of all or part of the research by the sponsor.

Unexpected events, due to which the study objectives are not likely to be met, may lead the sponsor to prematurely discontinue the study.

The sponsor reserves the right to discontinue the study at any time if the sponsor decides that the enrolment objectives have not been reached.

If the study is discontinued early, the information will be sent to the EC by the sponsor within 15 days.

# Data management

Data collected

The following data will be collected for each enrolled patient:

- Medical history
- Clinical examination
- Education
- Audiometry and visual examination results
- Speech therapy and psychological assessment results
- Educational background, social services management
- Results of the parental post-traumatic stress questionnaire

All data will first be collected through a paper questionnaire. The data will then be entered into an electronic case report form.

Right of access to the data

The investigators will provide the documents and individual data which are strictly necessary for follow-up, quality control and research audit to those who have access to these documents in accordance with current legislative and regulatory provisions (Articles L.1121-3 and R.5121-13 of the French Public Health Code).

Confidentiality

In accordance with the current legislative provisions (articles L.1121-3 and R.5121-13 of the French Public Health Code), those with direct access to the source data will take all necessary precautions to ensure the confidentiality of the information related to the research and to those involved, in particular as regards their identity and the findings. These individuals, and likewise the investigators themselves, are subject to professional secrecy.

Each patient will be assigned an identification code consisting of a site number and a patient number (3 digits).

The sponsor will ensure that each person involved in the research has given their approval in writing for access to individual data concerning them which is strictly necessary to check the quality of the research.

Archiving

The following documents regarding research are archived by the sponsor in compliance with Good Clinical Practices and current regulations for a period of 15 years after the end of research.

Control and Quality Assurance

Prior to the analysis of the data, screening for outliers, inconsistencies and missing data will be performed. The investigator will be contacted again for any corrections. There will be no on-site data monitoring.

An audit may be carried out at any time by individuals authorised by the sponsor and independent of the research managers. The purpose of the audit is to ensure the quality of the research, the validity of the results and that the applicable laws and regulations are respected.

The investigators agree to comply with the sponsor’s requirements and with the competent authority as regards any research audit or inspection.

# Statistical aspects

Assessment of the number of subjects to be recruited

Between 2010 and 2019, 169 cases of meningitis and meningococcal purpura fulminans were declared in the French National Observatory of Bacterial Meningitis in Children. The initial clinical data for these patients are already known. After having excluded deceased patients (n = 9) and patients who have been lost to follow-up (approximately 20%, n = 30), and with an envisaged acceptance rate of 80%, 100 patients should be enrolled and follow the care pathway established as part of the study.

Analyses

The proportion and confidence interval of children with sequelae will be described for the entire recruited cohort within each age group and according to the type of sequelae: neurological, orthopaedic, skin, sensory or developmental. The qualitative data will be described by their number and percentage. The quantitative data will be described by their median and standard deviation. Kaplan Meier survival curves will be drawn to determine the presence of sequelae at various times after meningitis. Comparison tests will be performed to determine the presence of sequelae according to their severity or the initial onset.

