| Inclusion criteria | - Infants and children 1 to 15 years of age - Having had meningitis or meningococcal purpura fulminans included in the observatory between 2010 and 2019 - Those with parental authority have read and understood the information letter and their express consent was obtained - Patient affiliated with a social security scheme (Social Security or French Universal Medical Coverage) | |
| Exclusion criteria | - Refusal of either parent | |
| Performance of the study | | |
| Patient pathway | [figure not shown] | |
| Study schedule | Planned start date of the study | Q4 2020 |
|  | Planned enrolment end date | Q2 2023 |
|  | Duration of the enrolment period | 2 years |
|  | Duration of patient follow-up in the study | 1 year |
|  |  | |
| Publications/Communications | Publication in a peer-reviewed medical journal  Presentation of the study (oral or poster) at a conference | |

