# Objectives of the research

Primary Objective

To assess the long-term (between one and ten years) physical, neurological or sensory sequelae from meningitis or meningococcal purpura fulminans.

Secondary Objectives

- Establish a course of care
- To assess medium/long-term post-traumatic stress on parents
- To assess the social impact of the disease: education of the children; activity of the parents

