# Subject screening

Inclusion criteria

- Infants and children 1 to 15 years of age;
- Who had meningitis or meningococcal purpura fulminans included in the observatory between 2010 and 2019;
- One of the individuals with parental authority has read and understood the information letter and their express consent has been obtained;
- Patient affiliated with a social security scheme (Social Security or Universal Medical Coverage).

Exclusion criteria

- Refusal of either parent.

Enrolment Objective

Approximately 100 patients are expected to be enrolled in the study.

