### Primary endpoint

- Number of children with at least one neurological, skin, orthopaedic or sensory sequela.

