**If the patient is not being monitored**:

Organisation of four visits with specialists within six months (max)

ENT Audiometry

Ophthalmologist

Psychologist

Tests according to age

Speech therapist

Tests according to age

Completion of the IES-R self-questionnaire

by the parents

Recovery of the results/assessments of the various specialists

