- - The **Vineland Scale** (behavioural assessment) can be performed for all ages and will be proposed for children for whom the WISC or WPPSI cannot be performed. Development will be measured on a development scale based on an interview with the parents.

Developmental age and standard deviation compared with chronological age.

Assessment duration: at least 1.5 hrs.

- **Ophthalmology assessment**

The examination will determine the presence of refraction disorders, strabismus,

amblyopia and/or ocular motor disorders.

An orthoptic assessment may potentially be necessary if it is prescribed by the ophthalmologist.

Assessment duration: 20 mins.

- **ENT assessment**

Performance of an audiogram (to be repeated if the audiogram was done more than one year previously).

Assessment duration: 10 mins.

- **Assessment of parental post-traumatic stress**

The IES-R is a validated, 22-question, self-administered questionnaire in French. It assesses the parent’s experience of their child’s disease and identifies the presence of post-traumatic stress (total score ≥33).

This survey will be offered online.

Research schedule:

| Enrolment start date: | Q4 2020 |
| --- | --- |
| Enrolment duration: | 24 months |
| Patient follow-up end date: | Q4 2023 |
| Date of publication of results: | Q2 2024 |
| Duration of subject participation: | 12 months |

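### Kaplan-Meier curves are planned for sequelae that have no onset date unless earlier records supply one, so part of the curve would follow visit dates

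*Protocol*

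**What the plan says.** Under Analyses (12.2) the protocol first plans proportions with confidence intervals for the whole cohort within each age group and by type of sequela. It then adds: "Kaplan Meier survival curves will be drawn to determine the presence of sequelae at various times after meningitis". It gives no event date and no censoring rule for these curves.

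The primary endpoint (7.1.1) is a status: "Number of children with at least one neurological, skin, orthopaedic or sensory sequela". The primary objective (5.1) is "To assess the long-term (between one and ten years) physical, neurological or sensory sequelae from meningitis or meningococcal purpura fulminans".

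Data collection works as follows:
- For a child not already followed, the pathway diagram (8.2.1) provides for "Organisation of four visits with specialists within six months (max").
- For a child already followed, earlier findings are retrieved and completed where needed (8.2.2). Assessments more than a year old are repeated (8.2.4).
- The visit schedule (8.2.3) marks the paediatric and neurological assessment at inclusion and again at the end of study visit. Participation lasts 12 months (8.3).
- The list of data collected (11.1) includes medical history and examination results, but no date of onset or first detection of a sequela.

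Section 12.2 also says: "The quantitative data will be described by their median and standard deviation".

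**The concern.** Kaplan-Meier needs, for each child, either the time at which the event occurred or a time up to which it is known not to have occurred. A sequela first found at a study visit supplies neither. It shows only that onset lay somewhere between the illness and the visit. If the visit date is entered as the event time, a deficit present since discharge is recorded as arising years later. The shape of the curve then depends on when children happened to be seen.

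There is also a mismatch of target. The sentence asks about presence at various times, which is prevalence. One minus Kaplan-Meier estimates cumulative first occurrence and cannot fall when a sequela resolves.

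At stake is how the time course is read. The expected results and the benefits section both mention that consequences may be delayed. A rising curve would look like support for that even if every sequela dated from the acute illness.

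**Working it through.** **Plan's own figures.** The protocol gives no event count, power or precision for the Kaplan-Meier analysis, so there is nothing to reproduce for it. The only related figure is the expected enrolment: (169 − 9 − 30) × 0.80 = 104, which the protocol gives as about 100. I use n = 100.

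**Time from disease to assessment.** Inputs: "Who had meningitis or meningococcal purpura fulminans included in the observatory between 2010 and 2019" (6.1), "Enrolment start date: | Q4 2020" (8.3) and "Planned enrolment end date | Q2 2023" (Project summary).
- Shortest: end of 2019 to Q4 2020, about 0.75 to 1 year.
- Longest at enrolment: start of 2010 to the end of Q2 2023, 13.5 years. If enrolment lasts 24 months from Q4 2020, it is about 13.0 years.

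The range is thus about 1 to 13 years, wider than the one to ten years in the objective.

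**Illustration in closed form.** Assumptions: a constant fraction p of children has a sequela from discharge, nothing changes later, and the visit time is uniform over 2 to 12 years. At time t the fraction not yet seen is (12 − t)/10. If every sequela is dated at the visit, the hazard is p/(12 − t), so

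S(t) = ((12 − t)/10)^p.

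If a fraction f is dated at discharge from records, the curve starts at pf. Among the remaining 1 − pf, the undated share is q = p(1 − f)/(1 − pf), so

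S(t) = (1 − pf) × ((12 − t)/10)^q.

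With p = 0.25 and f = 0.80: pf = 0.20 and q = 0.05/0.80 = 0.0625.

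| Years since disease | True prevalence | 1 − S, all dated at visit | 1 − S, 80% dated from records |
|---|---|---|---|
| 3 | 25% | 1 − 0.9^0.25 = 2.6% | 1 − 0.80 × 0.9^0.0625 = 20.5% |
| 5 | 25% | 1 − 0.7^0.25 = 8.5% | 1 − 0.80 × 0.7^0.0625 = 21.8% |
| 10 | 25% | 1 − 0.2^0.25 = 33.1% | 1 − 0.80 × 0.2^0.0625 = 27.7% |
| 11.9 | 25% | 1 − 0.01^0.25 = 68.4% | 1 − 0.80 × 0.01^0.0625 = 40.0% |

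The curve lies below the truth early and above it late.

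**Check on the protocol's own calendar.** This was simulated with n = 100 and 1,500 repetitions, disease dates uniform over 2010 to 2019, and visits uniform from Q4 2020 to the end of Q2 2023. The prevalence range is the 10 to 40% that section 4.2 reports at the end of hospitalisation, used here only as an assumption. Entries are mean 1 − S.

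| True, constant | All at visit: 5 y | All at visit: 10 y | 80% from records: 5 y | 80% from records: 10 y |
|---|---|---|---|---|
| 10% | 3.4% | 14.2% | 8.8% | 11.2% |
| 20% | 6.4% | 26.5% | 17.4% | 21.8% |
| 30% | 9.7% | 37.5% | 26.2% | 32.8% |
| 40% | 12.7% | 46.4% | 34.6% | 43.3% |

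About 21% of children are assessed beyond 10 years, where the curve continues to climb. At a true 30% with 80% dated from records, it runs from 24% to 49%. Only when every sequela is dated from records does it stay flat at the true value.

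**The case against.** The strongest reply is that these are not pure current-status data, and that stands. The enrolment interview covers skin sequelae and hospitalisations since the illness. Consultation, hospitalisation and imaging reports are collected, earlier findings are retrieved for children already followed, and section 12.2 says the initial clinical data are known. Section 4.1 already counts 36 short-term sequelae among 169 cases (36/169 = 21%). Many sequelae present at discharge, amputations among them, could therefore be dated early, and the artefact shrinks as the table shows. The 68% at 11.9 years should not be used as a headline: it dates every sequela at the visit and sits where 1% of children, about one in 100, remain unseen.

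A second reply is that a statistical analysis plan could define the event date. That helps for sequelae on record. For one first found at the study visit, no definition supplies the missing date. Using the visit date gives the artefact, and using the discharge date assumes the answer. Section 4.1 says that some children had sequelae not identified at discharge, and these are the ones least likely to be dated.

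Two stronger readings go too far. A reader might infer that each child is examined only once. That fits the specialist round, but the paediatric assessment is marked twice, though two looks within 12 months do not date an onset years before. A reader might also infer that the curve carries the study's central claim. No objective or endpoint concerns time to onset, and delayed consequences appear only as background under expected results and benefits.

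**Conclusion.** The concern holds in a limited form. The protocol names a time-to-event method for sequelae, and those first found at the study visit have no event time. For that subset the curve follows visit dates. Kaplan-Meier also answers a different question from the presence that the sentence names.

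The size depends on how many sequelae earlier records can date, which the protocol does not say. Against a true constant 25%, the illustration gives 33% at 10 years with none dated, about 28% with 80% dated, and 25% with all dated. The prevalence, the uniform visit times and the 80% are assumptions. The direction does not depend on their exact values as long as some sequelae are dated at the visit.

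It would be tempting to conclude that the main result is compromised. The documents do not support that: the primary endpoint is a count, reported as a proportion with a confidence interval, and Kaplan-Meier does not enter it. The sentence should be corrected, but the damage is confined to the descriptive time course.

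Pairing the median with a standard deviation is a separate and minor reporting point.

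**What to change.** Replace the Kaplan-Meier sentence in 12.2 with the prevalence of sequelae and its 95% confidence interval by band of time since infection. This answers the stated question with data already collected.

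If a cumulative-onset curve is still wanted, choose one of two routes and say which:
- an interval-censored or current-status (Turnbull) estimator, with the statement that it assumes sequelae do not resolve; or
- Kaplan-Meier restricted to sequela types with a documented onset date.

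Separately, pair the median with quartiles instead of a standard deviation.

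The cost is two sentences of text and the loss of a familiar curve. Precision within bands will be poor. With four equal bands of 25 children (an assumption) and a prevalence of 25%, the approximate half-width is 1.96 × √(0.25 × 0.75/25) = 17 percentage points, against 1.96 × √(0.25 × 0.75/100) = 8.5 for the whole cohort. That width reflects what about 100 children can show about timing.

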# Ethical and legal aspects

Legal obligations

The sponsor and the individuals who direct and monitor the research undertake to ensure that this research is performed in accordance with law No. 2012-300 of 5 March 2012 relating to public health policy and current regulatory provisions. (Articles L1121-1, paragraph 2 and R1121-3 of the French Public Health Code).

The research is conducted in accordance with this protocol.

Sponsor

The Intercommunal Hospital of Créteil (CHIC) is the sponsor of this research.

EC submission

This clinical trial received a favourable opinion from the Sud Méditerranée 1 [South Mediterranean 1] EC on 22/12/2020.

Substantial amendments

Requests for substantial amendments will be sent to the sponsor for the opinion of the relevant ethics committee.

The amended protocol should be the subject of an updated version and should be dated.

The information sheets and patient consent forms should be amended, if necessary.

Computerised data — French Data Protection Authority (CNIL)

Data processing will be performed under the confidentiality conditions defined by deliberation No. 2018-153 of 3 May 2018 amending the baseline methodology for personal data processing performed as part of research involving human subjects (MR-001).

Insurance

The Sponsor, CHI Créteil, declares that they have taken out an insurance policy with SHAM, policy No. 102.760, which covers the financial consequences of their civil liability resulting from the application of article L 1121-10 of the French Public Health Code in accordance with the clauses provided in the contract and within the set amounts.

# Publication rules

Scientific communications

Any written or oral communication of the research results must receive prior approval from the sponsor and the coordinating investigator.

The main results of this study will be published in an international peer-reviewed journal in English. The members of the scientific committee and the investigators will be mentioned on original and associated publications.

SANOFI’s financial support for this trial will be mentioned.

Communication of the results to the participants

Participants shall be informed, on demand, of the overall findings of the research in compliance with law No. 2002-303 of 4 March 2002.

Data transfer

The Créteil CHI is the owner of the data.

The conditions under which all or part of the research database are transferred are decided by the research sponsor and are subject to a written contract.

